## Abstract

**Background:**

Globally, suboptimal vaccine coverage is a public health concern. According to Uganda’s 2016 Demographic and Health Survey, only 49% of 12- to 23-month-old children received all recommended vaccinations by 12 months of age. Innovative ways are needed to increase coverage, reduce dropout, and increase awareness among caregivers to bring children for timely vaccination.

**Objective:**

This study evaluates a personalized, automated caregiver mobile phone–delivered text message reminder intervention to reduce the proportion of children who start but do not complete the vaccination series for children aged 12 months and younger in select health facilities in Arua district.

**Methods:**

A two-arm, multicenter, parallel group randomized controlled trial was conducted in four health facilities providing vaccination services in and around the town of Arua. Caregivers of children between 6 weeks and 6 months of age at the time of their first dose of pentavalent vaccine (Penta1; containing diphtheria, tetanus, pertussis, hepatitis B, and Haemophilus influenzae type b antigens) were recruited and interviewed. All participants received the standard of care, defined as the health worker providing child vaccination home-based records to caregivers as available and providing verbal instruction of when to return for the next visit. At the end of each day, caregivers and their children were randomized by computer either to receive or not receive personalized, automated text message reminders for their subsequent vaccination visits according to the national schedule. Text message reminders for Penta2 were sent 2 days before, on the day of, and 2 days after the scheduled vaccination visit. Reminders for Penta3 and the measles-containing vaccine were sent on the scheduled day of vaccination and 5 and 7 days after the scheduled day. Study personnel conducted postintervention follow-up interviews with participants at the health facilities during the children’s measles-containing vaccine visit. In addition, focus group discussions were conducted to assess caregiver acceptability of the intervention, economic data were collected to evaluate the incremental costs and cost-effectiveness of the intervention, and health facility record review forms were completed to capture service delivery process indicators.

**Results:**

Of the 3485 screened participants, 1961 were enrolled from a sample size of 1962. Enrollment concluded in August 2016. Follow-up interviews of study participants, including data extraction from the children’s vaccination cards, data extraction from the health facility immunization registers, completion of the health facility record review forms, and focus group discussions were completed by December 2017. The results are expected to be released in 2021.

**Conclusions:**

Prompting health-seeking behavior with reminders has been shown to improve health intervention uptake. Mobile phone ownership continues to grow in Uganda, so their use in vaccination interventions such as this study is logical and should be evaluated with scientifically rigorous study designs.

**Trial Registration:**

ClinicalTrials.gov NCT04177485; https://clinicaltrials.gov/ct2/show/NCT04177485

**International Registered Report Identifier (IRRID):**

DERR1-10.2196/17262

## Introduction

### Vaccination Coverage

Although global childhood routine vaccination coverage has increased markedly since the inception of the Expanded Program on Immunization (EPI) in 1974, coverage has plateaued since 2010, with rates of the third dose of diphtheria being between 84% and 86% [1]. According to Uganda’s 2016 Demographic and Health Survey (DHS), 49% of children aged 12 to 23 months received all recommended vaccinations by 12 months of age. Despite high coverage (95%) for the first dose of pentavalent vaccine (Penta1; containing diphtheria, tetanus, pertussis, hepatitis B, and *Haemophilus influenzae* type b antigens), which is given at 6 weeks of age, vaccination coverage for the third dose of pentavalent vaccine (Penta3), which is given at 14 weeks of age, was found to be 79% for a Penta1-Penta3 dropout of 17% [2]. Timely dosage of these vaccines remains low, threatening the health of Ugandan children with morbidity and mortality from vaccine-preventable diseases.

Innovative ways are needed to increase coverage, including increasing the recall rates of caregivers to bring children for timely vaccination [3]. Prompting health-seeking behavior via mobile technology interventions has been shown to improve health intervention uptake, particularly in high-income countries [4]. However, only a limited number of studies have evaluated the role of reminders sent by mobile phone text messages to increase vaccination coverage in low- and middle-income countries (LMICs).

### Background on Texting Reminders for Vaccination in LMICs

A few studies in LMICs [5-8] have assessed coverage improvements from the implementation of electronic immunization registers (EIRs) that had an automated text message reminder feature. The study designs varied in terms of scientific rigor and each concluded that coverage increased; however, it was not possible to assess the impact of text message reminders alone, as the EIRs provided the additional intervention of improving the tracking of individuals.

Other studies [9-14] enrolled participants between birth and Penta1 and followed them through Penta3, or in some cases through 12 months of age. Most of these studies focused on coverage at 2 to 4 weeks after the scheduled Penta3 date, as compared with the Kenya cluster randomized controlled trial (cRCT) [13], as it assessed coverage at 12 months of age, which is a typical EPI indicator. This cRCT study did not find the text message reminder intervention alone to significantly improve vaccination coverage at 12 months of age, likely due to high coverage in the control group. However, other studies concluded that text message reminders significantly improved vaccination coverage.

In addition, a few studies have focused primarily on the acceptability of text message reminders for vaccination [15-17]. Crawford et al [15] and Brown et al [16] found the acceptability to be high (99% and 95%, respectively); however, one study in Nigeria [17] found that only 69% of caregivers were willing to receive text message reminders.

Despite a body of research focused on vaccination reminders, there is still a deficit of scientifically rigorous studies evaluating the impact and scalability of text message reminders in LMICs. With 74% of households reported to have mobile phones [2], this research builds upon a growing mobile health (mHealth) system in Uganda to use personalized, automated text messages to remind caregivers of upcoming vaccination visits, which is hypothesized to reduce vaccination dropout (defined as starting but not completing the recommended vaccination schedule) in children under 12 months and to eventually contribute to reductions in morbidity and mortality due to vaccine-preventable diseases. With the goal of being scalable if shown to be effective, this intervention is designed to assess the impact of text message reminders using an mHealth platform already implemented in Uganda.

### Study Objectives

Primary objective:

To evaluate a personalized, automated caregiver text message reminder intervention to reduce vaccination dropout for children aged 12 months and younger in select health facilities in Arua district

Secondary objectives:

To measure the impact of a personalized, automated caregiver text message reminder intervention to increase the probability that children will receive Penta3 within 12 weeks of Penta1 receipt and MCV by 10 months of age.To assess caregiver acceptability of a personalized, automated caregiver text message reminder interventionTo determine the cost-effectiveness of a personalized, automated caregiver text message reminder intervention from the provider (Ministry of Health [MOH]) perspective

## Methods

### Study Design

A two-arm, multicenter, parallel group randomized controlled trial (RCT) was conducted in 4 health facilities providing vaccination services in and around the town of Arua. Caregivers were recruited at the time of their children’s Penta1 vaccination visit. Caregivers and their children were randomized to either the intervention arm or the control arm and followed until the exit interview, which took place at the health facility during the children’s measles-containing vaccine (MCV) visit or outside the health facility (generally at the caregiver’s home) after the last child in the study completed 1 year of age. If the original caregiver was not available at the exit interview, another caregiver was consented and interviewed if available. The protocol was designed taking into consideration criteria described by the Consolidated Standards of Reporting Trials (CONSORT) [18], and the diagram of the study design is shown in Figure 1.

**Figure 1 figure1:**
[figure not shown]
Diagram of study design.

### Setting and Participants

Districts located in Uganda but outside the city of Kampala were considered for inclusion in the study if they had the following characteristics:

Penta1 administrative coverage ≥80% (calculated as the number of children vaccinated with Penta1 vaccine divided by the total number of eligible children)Penta1-MCV administrative dropout rate ≥10% (calculated as the number of children vaccinated with the Penta1 vaccine minus the number of children vaccinated with MCV, divided by the number of children vaccinated with Penta1)Interest from District Health OfficeBoth urban and rural populations

Among the districts under consideration, Arua district was selected as the study area because it had a Penta1 administrative coverage of over 80% and a Penta1-MCV dropout rate greater than 10%. We used this parameter for dropout because 10% is considered the programmatic threshold for unacceptable dropout [19]. In December 2014, we conducted a site visit to the health facilities in and around Arua town, where we found that 18 out of 25 caregivers (72%) either had mobile phones with them or knew the phone numbers of their family phones. In addition, most caregivers indicated that they had village-level mobile phone reception as well as an electrical source to charge their phones (most typically solar charge).

Arua district is in northwest Uganda and borders the Democratic Republic of Congo in the west. Arua has an estimated population (2014) of 782,077, with an under 1-year-old target population of 28,605 [20]. Arua has 72 health facilities with varying levels of health services that are provided, including 3 hospitals.

To maximize study personnel efficiency, the 4 largest health facilities in and around Arua town were approached, and they agreed to participate as enrollment sites. Of these 4 facilities, 2 vaccinated every day, 1 vaccinated twice per week, and 1 vaccinated once per week. All 4 facilities provided outreach vaccination on an irregular basis.

During the enrollment period (February-July 2016), all caregivers who attended one of the selected health facilities for their children’s Penta1 vaccinations were approached to determine if they met the inclusion criteria and were willing to participate.

Caregiver participant inclusion criteria were as follows: had access to a personal or household mobile phone that could receive text messages; caregiver for a child between 6 weeks and 6 months of age at the time of Penta1 vaccination visit; lived in Arua district; and was 14 years of age or older.

Caregiver participant exclusion criteria were as follows: did not have access to a mobile phone number at the time of enrollment; did not agree or was unable to consent to participate in the study; did not anticipate being the caregiver through the child’s first birthday; planned to move out of Arua district in the upcoming year; prior enrollment of the caregiver with a different child.

Illiterate caregivers who were interested in participating, gave informed consent, and met the other inclusion criteria were enrolled. The understanding was that illiterate participants would have family members or friends read the text messages to them.

### Study Arms

The study consisted of 2 arms: a control arm and an intervention arm. The control arm received the standard of care in the selected health facilities, defined as health workers providing child vaccination home-based records (HBRs), known as Child Health Cards in Uganda, to caregivers, as available and providing verbal instruction of when to return for the next visit. The intervention arm received the standard of care as well as personalized, automated text message reminders sent to participants for each of their 3 subsequent vaccination visits, as per the Uganda National EPI schedule [21] (Table 1).

**Table 1 table1:** Uganda National Expanded Program on Immunization schedule in 2016-2017.

Vaccination visit	Age	Vaccines
0	Birth	Bacillus Calmette-Guerin Vaccine OPV^a^ birth dose
1	6 weeks	Penta1^b,c^ OPV1 PCV1^d^
2	10 weeks	Penta2 OPV2 PCV2
3	14 weeks	Penta3 OPV3 PCV3 IPV^e,f^
4	9 months	MCV^g^

^a^OPV: oral polio vaccine.

^b^Penta1: pentavalent vaccine first dose.

^c^Pentavalent vaccine contains diphtheria, tetanus, pertussis, hepatitis B, and *Haemophilus influenzae* type b antigens.

^d^PCV1: pneumococcal conjugate vaccine first dose.

^e^IPV: inactivated polio vaccine.

^f^IPV was introduced in April 2016.

^g^MCV: measles-containing vaccine.

### Enrollment, Randomization, and Blinding

Study personnel were stationed in the 4 selected health facilities and recruited caregivers of children between 6 weeks and 6 months of age who presented for their Penta1 vaccinations. Study personnel explained the study, obtained consent, and enrolled the eligible caregivers who agreed to participate in the study. Study participants responded to a brief preintervention questionnaire to collect basic demographic information and locating information. The health facility staff vaccinated the children, filled out the health facility immunization register, and filled out the children’s HBRs per standard practice in Uganda [22]. For each study participant, the study personnel sent a text message to a designated short code number with information that included the caregiver’s preferred first or last name, caregiver’s mobile phone number, child’s date of birth, and the participant study ID in the following format: “Penta [ChildDOB] CN.[CaregiverName].PN.[PhoneNumber].ID. [StudyID]” (Figure 2).

**Figure 2 figure2:**
[figure not shown]
Screenshot of mobile phone displaying data registration format used at health facility study sites in Arua, Uganda.

The information in the text message populated a centralized immunization registry database in a District Health Information System 2 (DHIS2) Software (version 2.26) Tracker Module instance created for this study. In addition, the mobile phone number of the study personnel who registered the study participant and the date that the registration text message was sent (which also served as the date of Penta1 vaccination) were recorded in the database. At the end of each day, study participants who were registered that day were randomized by computer using stratified permuted block randomization to either the control or the intervention arm, which was then recorded in the database as well. For randomization assignment, study participants were matched in order of registration to a sequence generated by nonfield study personnel before the start of enrollment. Stratification and blocking occurred at the health facility level; blocks of random size were used (lengths=2, 4, and 6) to minimize the ability to predict the next assignment. The health worker, study personnel, and participants were blinded to the randomization at assignment. However, unblinding of the intervention group occurred when they received the first text message reminder. The control group became unblinded, as they realized that they were not receiving text message reminders. On occasion, study participants shared their intervention status with health workers and field-level study personnel, thus unblinding them to the status of some caregivers. Nonfield staff study personnel who managed the database had access to intervention status after randomization assignment.

### Texting Reminder Intervention

Following the Uganda EPI schedule and accounting for health worker practices in Arua, the DHIS2 Tracker instance was programmed to automatically schedule follow-up vaccination visits at 30 days after Penta1 (for the visit to receive Penta2, oral polio vaccine [OPV] dose 2, and pneumococcal conjugate vaccine [PCV] dose 2), 61 days after Penta1 (for the visit to receive Penta3, OPV3, and PCV3), and 274 days after the child’s date of birth (for MCV). For each scheduled follow-up vaccination visit, the DHIS2 Tracker queued text message reminders to be sent on 3 different dates. At 7 AM on the scheduled dates, the DHIS2 Tracker delivered the messages to an SMS text message aggregator in Uganda, which then routed the messages to the appropriate Uganda telecommunications service providers, which in turn sent the messages to the appropriate participants. Every intervention group participant received the reminder in both English and Lugbara (the most common local language spoken in Arua). Penta2 text message reminders were sent 2 days before, on the day of, and 2 days after the scheduled vaccination visit. Penta3 and MCV text message reminders were sent on the scheduled day of vaccination and five and seven days after. Compared with the Penta2 text message reminders, the Penta3 and MCV text message reminders were sent later because at the time of reminder scheduling, the exact due dates for Penta3 were unknown (because Penta2 had not yet been received) and MCV (because DHIS2 Tracker could only schedule in terms of days, not months). Later reminders were preferred to reduce the possibility that caregivers would present too early for vaccination. As an automated intervention, text message reminders were sent regardless of whether the caregiver had already visited the health facility. Ideally, the visit for Penta3, OPV3, and PCV3 should have been scheduled 30 days after the visit for Penta2, OPV2, and PCV2. However, as the DHIS2 Tracker instance was not updated after vaccination visits, we had to schedule the visit in reference to the date of the visit for Penta1, OPV1, and PCV1.

Before study enrollment, consensus decision making with caregivers and health workers in Arua district and partners at the national level took place to finalize the pattern, timing, and exact wording of the text messages (Table 2). As some text message reminders would be automatically sent to caregivers either before the child was due for vaccination or after a completed visit, we emphasized in the text messages that the caregiver refer to the child’s HBR to confirm the date of the next vaccination.

**Table 2 table2:** Content and timing of mobile phone text message reminders sent to intervention group participants’ mobile phones.

Vaccination visit, scheduled vaccination visit^a^, and message timing			Message^b^

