For the primary objective, a logistic regression model with fixed effects at the health facility level will be used to analyze differences between intervention and control groups in Penta3 and MCV coverage at 12 months of age. For the assessment of timeliness, a logistic regression model with fixed effects at the health facility level will be used to analyze differences between intervention and control groups in Penta3 coverage 12 weeks after receiving Penta1 and MCV coverage at 10 months of age. In addition, Cox proportional hazards models with fixed effects at the health facility level will be used to analyze time-to-event (ie, timeliness) outcome data. The primary analyses will be based on intention-to-treat, but per-protocol analysis will also be conducted. Dates of vaccination from HBRs will be used for analysis, supplemented with dates from the immunization register extraction if HBR dates are unavailable. In addition to logistic regression, log-binomial regression models will be used to estimate risk ratios. Data will be analyzed using statistical software such as STATA, SAS, or R.

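### The timeliness endpoints and Cox models set no lower time limit, although Penta3 reminders can precede the due date when Penta2 is late, so a too-early dose counts in favour of the arm that gets the reminders

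*Protocol article*

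**What the plan says.** The secondary objective (Study Objectives) is to "increase the probability that children will receive Penta3 within 12 weeks of Penta1 receipt and MCV by 10 months of age". The analysis section (Data Management and Analysis) repeats the same two cut-offs for the logistic models, "Penta3 coverage 12 weeks after receiving Penta1 and MCV coverage at 10 months of age", and adds that "Cox proportional hazards models with fixed effects at the health facility level will be used to analyze time-to-event (ie, timeliness) outcome data". No minimum age, minimum interval or start of eligibility is stated for either analysis.

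Under Texting Reminder Intervention, the Penta3 visit is scheduled "61 days after Penta1 (for the visit to receive Penta3, OPV3, and PCV3"), with messages on that day and 5 and 7 days later. The section explains that the tracker was not updated after visits, so the Penta3 date had to be set from Penta1, although 30 days after the Penta2 visit would have been ideal. It concedes that "some text message reminders would be automatically sent to caregivers either before the child was due for vaccination or after a completed visit". Two safeguards are described: the Penta3 and MCV messages were placed late ("Later reminders were preferred to reduce the possibility that caregivers would present too early for vaccination"), and the messages tell the caregiver to check the date on the child's card.

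**The concern.** The protocol identifies early presentation as something its reminders might provoke, yet the endpoints it fixes cannot register it. A Penta3 given too soon after Penta2 scores as a timely dose in the logistic model if it falls by day 84, and as an earlier event in the Cox model. Control children receive no reminders, so any short-interval doses that the messages lead to would arise in the intervention arm only. The timeliness comparison could then mix two effects that should be kept apart: children brought on time, and children brought too early. What is at stake is the interpretation of a secondary objective.

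**Working it through.** **Inputs.** Penta2 is scheduled on day 30 after Penta1, with reminders on days 28, 30 and 32. Penta3 is scheduled on day 61, with reminders on days 61, 66 and 68. MCV is scheduled on day 274 of age, with reminders on days 274, 279 and 281 (Texting Reminder Intervention; Table 2). The Table 1 ages of 6, 10 and 14 weeks are 4 weeks (28 days) apart; the text gives 30 days as the ideal gap from Penta2 to Penta3. The Penta3 limit is 12 × 7 = 84 days after Penta1.

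**Penta3, child on schedule.** At 4-week spacing Penta3 is due on day 56, so the reminders come 61 − 56 = 5, 66 − 56 = 10 and 68 − 56 = 12 days after the due date. With Penta2 on day 30 and a 30-day gap it is due on day 60, and all three reminders still follow it. These children get no early prompt.

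**Penta3, late Penta2.** A reminder on day r is early if Penta2 day + gap > r, that is, if Penta2 came after day r − gap.

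| Reminder day | Early if Penta2 after (28-day gap) | Early if Penta2 after (30-day gap) |
|---|---|---|
| 61 | day 33 | day 31 |
| 66 | day 38 | day 36 |
| 68 | day 40 | day 38 |

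**When the binary endpoint is affected.** A full-interval Penta3 can fall within the limit only if Penta2 came by day 84 − 28 = 56 (or 84 − 30 = 54). If Penta2 came on days 41 to 56, all three reminders are early, but the full-interval date is days 69 to 84, still inside the limit. A short-interval dose there adds to the timely proportion only if the child would otherwise have missed day 84. If Penta2 came after day 56, a Penta3 scored as timely must be a short-interval dose. In the Cox model any earlier dose is an earlier event, whichever case applies.

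**MCV.** Over births from 1 August 2015 to 20 July 2016 (an assumed range of 355 dates, inferred from the enrolment period and eligible ages), 274 days minus nine calendar months is −2 for 28 dates, −1 for 92, 0 for 204 and +1 for 31. The first reminder is therefore 1 to 2 days early for (28 + 92)/355 = 34% of dates. Nine months is at most 276 days, so the reminders on days 279 and 281 are never early.

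**How much a small shift would matter (assumption only).** Take 838 per arm. This is the protocol's figure for MCV dropout; it reproduces as one-sided 5%, 90% power, 84% against 89%, with continuity correction. Suppose no true effect, control timeliness of 60 to 80%, and x net extra points from short-interval doses in children who would otherwise have missed the limit. The chance of a two-sided .05 result favouring the intervention is Φ[(x − 1.96·SE₀)/SE₁], with SE₀ pooled and SE₁ unpooled. For example, with 60% against 62%, SE₀ = √(2 × 0.61 × 0.39/838) = 0.0238 and SE₁ = √((0.60 × 0.40 + 0.62 × 0.38)/838) = 0.0238, giving Φ(−1.12) = 13%.

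| Net extra points | Chance of an apparent benefit |
|---|---|
| 0 | 2.5% |
| 1 | 6–7% |
| 2 | 13–18% |
| 3 | 24–35% |
| 5 | 56–77% |

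Nothing in the documents says which row applies.

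**The case against.** The strongest reply is that an early message is not an early dose. It becomes one only if Penta2 was late, the caregiver does not act on the card, and the health worker vaccinates before the due date. The late placement of the Penta3 and MCV messages works for children on schedule, and every message points to the card. This stands as far as it goes. The safeguards are partial, however: later timing does not protect a child with a late Penta2, cards are given only where available (Study Arms), caregivers who cannot read are enrolled (Setting and Participants), and lost cards are anticipated (Sample Size).

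A reader might infer that the reminders did cause premature doses and that the timeliness effect is inflated by some known amount. The documents support neither: they report no early dose and no distribution of Penta2 dates. Multiplying a guessed share with late Penta2 (say 10–30%) by a guessed share vaccinated early (5–20%) gives 0.5–6 points. That would count short-interval doses, not inflation of the binary endpoint, and the 5-point planning difference concerns MCV dropout, a different endpoint.

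It can also be said that dose-validity rules belong in an analysis plan, which is not shown. One may exist there. But the article states the endpoint limits in both the objective and the analysis section, and as stated they admit doses given too early.

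Finally, Table 1 gives ages rather than minimum intervals, and children could enrol at up to 6 months of age, so the 28-day gap is an inference from the spacing of those ages. This is correct; the cut-offs move by 2 days if the protocol's 30 days is used.

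**Conclusion.** The point holds as a weakness in the definition of a secondary objective. As written, a dose given before it is due is scored as timely or as an earlier event, and only one arm receives prompts that can precede the due date. It concerns mainly Penta3 in children with a late Penta2 (after day 33 for one early reminder and after day 40 for all three, at 4-week spacing). The endpoint definition itself breaks down when Penta2 came after day 56. The direction of any bias would favour the intervention; its size cannot be derived from the documents and may be negligible. The MCV part is minor, at most 2 days on the first reminder only. The primary analysis of 12-month coverage and the sample size are not touched.

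**What to change.** 1. Add a lower bound to each timeliness endpoint, taken from the national schedule that the protocol cites. First reconcile the 4-week spacing of the Table 1 ages with the 30 days in Texting Reminder Intervention. Because children enrol at different ages, the Penta3 bound needs to be an interval from Penta2, with a stated rule for a missing Penta2 date. All randomised children stay in the denominator.
2. In the Cox models, run time from a baseline origin (Penta1 date for Penta3; birth or enrolment for MCV) and count the first dose that meets the bound. Do not start time at risk at the due date derived from Penta2: that date arises after randomisation and is itself a target of the reminders, so it would exclude children without Penta2 and could select differently by arm.
3. Report the number and proportion of early doses by arm.
4. Keep the present definition, with an upper limit only, as a sensitivity analysis.

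The cost is endpoint wording and some programming. Vaccination dates are extracted from cards and registers, the birth date is recorded at registration, and the Results section still describes the analysis as to be done. The price may be a slightly smaller timeliness effect. If early doses prove rare, the by-arm table will show it.
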